### Visit schedule and assessments

2.13

At Visit 1 and Visit 7, the following will be recorded: patient demographics, medical history, concomitant medications, vital signs, physical examination, as well as assessments including cardiopulmonary exercise testing (CPET), N-terminal pro-brain natriuretic peptide (NT-proBNP), echocardiography, 6MWT, NYHA functional class, EQ-5D score, TCM syndrome score, coagulation function, routine blood, urine, and stool tests, urine pregnancy test, liver and kidney function tests, electrocardiogram (ECG), chest CT (only at Visit 1), and others. At Visit 2, randomization numbers will be assigned, the investigational drug or placebo will be randomly dispensed, and concomitant medications will be recorded. At Visit 1 and Visit 5, the following assessments will be performed: CPET, NT-proBNP, echocardiography, coagulation function, urine pregnancy test, and chest CT (only at Visit 1). At Visit 1, Visit 3, and Visit 5, the following assessments will be performed: 6MWT, NYHA functional class, EQ-5D score, TCM syndrome score, routine blood, urine, and stool tests, liver and kidney function tests, electrocardiogram (ECG), and others. At Visit 1, Visit 3, Visit 4, Visit 5, and Visit 6, major symptoms and signs will be recorded. Adverse events (AEs) and serious adverse events (SAEs) will be monitored and recorded throughout the trial. See Table 3 for the visit schedule and assessments.

**Table 3 T3:** Visit schedule and assessments.

Assessment items	Study phase	Screening period	Enrollment period	Treatment period				
	Visit	1	2	3	4	5	6	7
	Week	-1W	0W	4W ± 3D	8W ± 3D	12W ± 3D	18W ± 3D	24W ± 3D
Screening of participants		√						
Signing of informed consent		√						
Medical interview	General information	√						
	Medical history	√						
	Concomitant medications	√	√	√	√	√	√	√
	Vital signs	√		√		√		√
	Physical examination	√		√		√		√
Efficacy measures	Peak VO_2_	√				√		√
	NT-proBNP	√		√		√		√
	Echocardiography	√				√		√
	NYHA class	√		√		√		√
	6MWT	√		√		√		√
	TCM syndrome scale	√		√		√		√
	Major symptoms/signs	√		√	√	√	√	√
	EQ-5D score	√		√		√		√
	Coagulation function	√				√		√
Safety measures	Routine blood test	√		√		√		√
	Routine urinalysis	√		√		√		√
	Routine stool test+occult blood^a^	√		√		√		√
	Liver function test	√		√		√		√
	Kidney function test	√		√		√		√
	Urine pregnancy test	√				√		
	Electrocardiogram (ECG)	√		√		√		√
	Chest CT	√						
Wearable monitoring devices			√	√	√	√	√	√
Multi-omics analysis		√						√
Inclusion criteria		√						
Exclusion criteria		√						
Screening number		√						
Randomization number assignment			√					
Dispensing of study drug and diary card			√	√	√	√	√	
Return of study drug and packaging				√	√	√	√	√
Return of diary card				√	√	√	√	√
Overall assessment	Adherence assessment			√	√	√	√	√
	Adverse event reporting and follow-up		√	√	√	√	√	√
	Efficacy assessment			√	√	√	√	√

a Perform stool routine and occult blood tests at Visits 1, 3, 5, and 7 when a bowel movement occurs or when the stool color is found to be black.

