### Laboratory thresholds and adverse event management measures

2.8

Laboratory abnormalities will be graded and recorded according to the Common Terminology Criteria for Adverse Events (CTCAE), Version 6.0, published by the US National Cancer Institute (NCI) (26). Any adverse events occurring during the trial, including subjective discomfort of subjects and laboratory test abnormalities, must be taken seriously, carefully analysed, and managed promptly to ensure subject safety. Should adverse events such as hepatic or renal dysfunction, bleeding risk, drug or food allergy, or gastrointestinal discomfort arise during the trial, appropriate measures—including symptomatic treatment, dose adjustment, treatment discontinuation, or observation—may be taken depending on the nature and severity of the event. Investigators are required to follow up all adverse events until they resolve to baseline, are assessed by the investigator as stable, or the subject is lost to follow-up or withdraws informed consent. All adverse events should be documented in the source medical records and the adverse event pages of the CRF to facilitate source data verification.

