#### Safety outcomes

2.14.3

Routine blood, urine, and stool tests, electrocardiogram (ECG), liver and kidney function tests.Urine pregnancy test (for women of childbearing potential).Chest CT.Adverse events (AEs) or serious adverse events (SAEs).

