The composition of SXYX follows a rigorous principle of herb compatibility. The sovereign herbs, raw *Hedysarum Multijugum Maxim*, *Codonopsis Radix*, and *Cimicifugae Rhizoma*, supplement Qi and elevate sunken Qi, and carry the effects of the formula upward. The minister herbs, *Radix Paeoniae Rubra*, *Curcumae Rhizoma*, *Trichosanthes Kirilowii Maxim*, *Allium Azureum Ledeb*, *Arum Ternatum Thunb*, and *Radix Bupleuri*, activate blood circulation and resolve stasis, as well as eliminate phlegm and remove turbidity. The assistant herbs, *Cinnamomi Ramulus* and *Lepidii Semen Descurainiae Semen*, unblock Yang, transform Qi, and promote diuresis; *Anemarrhenae Rhizoma* clears heat and nourishes Yin, counterbalancing the warm-dry nature of the Qi-supplementing herbs. The messenger herb, *licorice*, harmonizes the actions of the various ingredients and protects the middle burner (spleen and stomach). The overall effect of the formula is to supplement Qi and activate blood circulation, making it particularly suitable for treating HFpEF with the syndrome of Qi deficiency and blood stasis. HFpEF is secondary to comorbidity-driven systemic inflammation, progressive fibrosis, and myocardial cell injury (31). Preclinical evidence has suggested that flavonoids derived from *Astragalus membranaceus* inhibit Th1 and Th17 cell differentiation and increase regulatory T cell (Treg) levels, thereby reducing inflammatory damage (34). It has also been shown in animal studies that astragaloside IV and *Astragalus* polysaccharide (APS) regulate the aberrant activation of the TGF-β1/Smads pathway, downregulate p38 MAPK and NF-κB/p65 phosphorylation levels, and inhibit myocardial fibrosis (35). Additionally, studies based on isolated compounds have indicated that total paeony glycoside (TPG) inhibits the activation of the NLRP3 inflammasome and alleviates the inflammatory response (36). Similarly, experimental evidence suggests that the β-sitosterol component of Gualou Xiebai Banxia Decoction reduces the levels of IL-1β, IL-6, and TNF-α in endothelial cells, thereby inhibiting inflammatory responses, cardiomyocyte apoptosis, and myocardial fibrosis (37, 38). Preclinical data have also demonstrated that cinnamaldehyde exerts anti-inflammatory effects by modulating multiple signaling pathways, including TLR4, TRAF6, NF-κB, JAK/STAT, and Nrf2, through the regulation of inflammatory cytokines such as TNF-α, IL-1β, and IFN-γ (39). Furthermore, findings from rodent models suggest that the aqueous extract of *Lepidii Semen Descurainiae Semen* (Tinglizi) activates the PI3K/Akt/mTOR signaling pathway, inhibits apoptosis, and ameliorates ventricular remodeling in rats with heart failure (40). Finally, one preclinical study has shown that Shengxian Yixin Granule inhibits myocardial fibrosis, delays ventricular remodeling, and improves cardiac function in rats with myocardial infarction via the PI3K/AKT signaling pathway (41). Taken together, it may be hypothesized that SXYX could exert its therapeutic effects on HFpEF through multiple pathways, including the inhibition of inflammatory responses, myocardial fibrosis, and apoptosis. However, it is important to note that the above mechanistic evidence is primarily derived from individual herbs, isolated compounds, or animal models; these findings should be interpreted as providing biological plausibility rather than proof of the mechanism of action of the complete SXYX formula in patients with HFpEF. Confirmation of these mechanistic hypotheses in the current human trial is warranted.

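### Footnote a to Table 3 makes the scheduled stool and occult-blood test conditional while section 2.13 does not, so a listed safety outcome is selectively ascertained

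*Protocol article*

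**What the plan says.** Table 3 schedules the routine stool test with occult blood, as a safety measure, at Visits 1, 3, 5 and 7 (screening, then weeks 4, 12 and 24, the last three with a window of ±3 days). Footnote a limits it to those visits "when a bowel movement occurs or when the stool color is found to be black".

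The text of section 2.13 carries no such limit. For Visits 1, 3 and 5 it lists "routine blood, urine, and stool tests, liver and kidney function tests, electrocardiogram (ECG), and others" among the assessments to be performed, and it also lists stool tests for Visit 7.

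Section 2.14.3 makes stool testing part of a safety outcome: "Routine blood, urine, and stool tests, electrocardiogram (ECG), liver and kidney function tests". Section 2.8 names "hepatic or renal dysfunction, bleeding risk, drug or food allergy, or gastrointestinal discomfort" among the adverse events that might arise, and it counts laboratory abnormalities as adverse events. Section 2.18 compares adverse-event incidence between arms by chi-square or Fisher's exact test; the safety set is everyone who took a dose.

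**The concern.** An occult-blood test is meant to find bleeding that cannot be seen. Under the footnote, whether it is done depends on whether a stool is passed and on whether the stool already looks black. The first condition has nothing to do with bleeding but may be related to treatment, since the product is an oral granule taken three times daily. The second is a sign of the event being sought. A patient with hidden bleeding who meets neither condition leaves no result.

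Two things follow. Positives are under-counted by an unknown amount. And if the arms differ in how often a sample is available, the counts of positives can differ, or a real difference can be hidden, with blinding intact. A positive result that is recorded as an adverse event can also enter the section 2.18 comparison, while an untested patient contributes only the absence of an event. Because Visit 1 is conditional as well, some patients may lack the baseline result needed to call a later positive new.

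**Working it through.** **1. The passages side by side.** Table 3 and section 2.13 give fixed visits. Footnote a gives the same visits with two triggers joined by *or*. A patient with neither trigger is tested under section 2.13 and not tested under the footnote. Both cannot be followed.

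**2. How wide is the first trigger?** Suppose any bowel movement within the ±3-day window counts. A black stool is ordinarily seen only once it has been passed, so the second trigger would then add nothing. For it to have a purpose, the first trigger must be narrower, for example a movement during the visit itself. The article does not say which, so sites may apply it differently.

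**3. What selective testing can do.** The article states no figure on this point. The only input taken from it is 74 patients per arm (section 2.2: 59 ÷ 0.8 = 73.75, rounded up to 74). Everything else below is assumed. True positivity is the same in both arms throughout, so any difference comes from testing alone.

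*(a) One testing round.* Assume 5% truly positive, one in five of these visibly black and always tested, and the rest tested only if a movement occurs (probability p).

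Found = 0.05 × 0.2 + p × 0.05 × 0.8

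| p | Found | Missed, 1 − found/0.05 | Patients per 74 |
|---|---|---|---|
| 0.30 | 0.010 + 0.012 = 2.2% | 56% | 1.6 |
| 0.50 | 0.010 + 0.020 = 3.0% | 40% | 2.2 |
| 0.90 | 0.010 + 0.036 = 4.6% | 8% | 3.4 |
| 0.95 | 0.010 + 0.038 = 4.8% | 4% | 3.6 |

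With p = 0.30 against 0.50 the ratio is 3.0/2.2 = 1.36, a gap of about 0.6 of a patient per arm. With 0.90 against 0.95 the ratio is 4.8/4.6 = 1.04.

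*(b) Three post-baseline rounds (Visits 3, 5, 7), no dropout.* Let s be the probability of being tested at a visit and 5% the positivity per visit.

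Expected patients with a detected positive = 74 × [1 − (1 − 0.05 × s)³]

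s = 0.9 gives 9.5, s = 0.7 gives 7.5, s = 0.5 gives 5.4. The ratio is 1.76 for 0.9 against 0.5, 1.39 for 0.7 against 0.5, and 1.0 when testing is equal.

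*(c) Dividing by the number tested is not enough.* Assume 5% positive, of which 2 points are black stools that are always tested. Movement probability is 0.9 in one arm and 0.5 in the other.

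- 0.9: positives 0.02 + 0.03 × 0.9 = 0.047; tested 0.02 + 0.98 × 0.9 = 0.902; share 5.2%.
- 0.5: positives 0.02 + 0.03 × 0.5 = 0.035; tested 0.02 + 0.98 × 0.5 = 0.510; share 6.9%.

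If only samples taken regardless of colour are counted, the shares are 0.05 × 0.9/0.9 and 0.05 × 0.5/0.5, both 5%, provided positivity is unrelated to whether a stool is passed. So tests prompted by colour have to be kept apart from scheduled samples.

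**The case against.** The strongest reply is that the footnote is only a feasibility note: a stool test needs stool, the visits have a window, and sites will collect a sample when one is passed. On that reading few tests are missed and the arms hardly differ, as the 0.90 against 0.95 line shows. A condensed article may also leave collection details to the full protocol. Part of this stands: the article does not exclude a sample taken within the window, and the words *at the visit* are not in the footnote. But this reading makes the black-stool trigger redundant and leaves the mismatch with section 2.13. The fault lies in a rule that is stated, not in a detail left out.

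Three stronger readings should be resisted.

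- *That testing will differ by arm.* Section 2.8 gives a contingent list of events that might occur in any participant. It does not say the granule is expected to change bowel frequency, and no passage gives data on this.
- *That the trial's check for bleeding depends on bowel habit.* Routine blood tests (Visits 1, 3, 5, 7) and coagulation tests (Visits 1, 5, 7) do not depend on it, and "Adverse events (AEs) and serious adverse events (SAEs) will be monitored and recorded throughout the trial". The black-stool trigger adds tests and removes none.
- *That section 2.18 uses the wrong denominator for occult blood.* It describes only an adverse-event comparison. The denominator for stool results is ordinary content of an analysis plan, which is not shown.

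**Conclusion.** The point holds as a minor weakness in safety ascertainment. Footnote a and section 2.13 contradict each other, and under the footnote the occult-blood result is collected selectively, partly on a sign of the event itself. A difference between arms is possible only if sample availability differs between them, and the documents neither show nor exclude that.

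The size cannot be estimated, because positivity, the share of black stools and bowel frequency are all unstated. The ratios of 1.04 to 1.76 come entirely from the assumed testing probabilities; they show direction and sensitivity and do not predict this trial. In the one-round illustration with 0.30 against 0.50, the gap is less than one patient per arm. The primary endpoint, peak VO₂, is not touched.

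**What to change.** Reconcile footnote a with section 2.13. Have every patient provide one stool sample within the existing ±3-day window of Visits 3, 5 and 7, and one during screening before Visit 2, whatever the stool colour.

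Report the number tested by arm and visit. Tabulate extra tests prompted by black stool separately; a scheduled sample that happens to be black stays with the scheduled samples.

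The cost is a change of footnote wording, a sample container and a slight burden on patients. The tests are already scheduled, and the reporting change needs no new data.

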### Outcome measures

2.14

#### Primary outcome

2.14.1

Change from baseline to 24 weeks in peak VO_2_ as assessed by CPET.

#### Standard operating procedure (SOP) for cardiopulmonary exercise testing (CPET)

2.14.1.1

Based on the references (29, 30), the following detailed rules have been formulated.
Standardised CPET protocol and equipment calibration: All participating centres will employ a computer-controlled, individualised ramp protocol, with the duration of each test controlled within 8–12 min. A cycle ergometer is preferred as the testing device; if treadmill testing is used, strict calibration of speed and grade increments is required. To ensure the integrity and reliability of the data, biochemical calibration of the gas analysers and flow sensors is performed before each test, using standard calibration gas mixtures and a 3-L calibration syringe.Standardised criteria for maximal exertion and data processing: A test is deemed a maximal exercise test only if the participant meets at least one of the following criteria: peak respiratory exchange ratio (RER) ≥1.10, and/or heart rate reaching ≥85% of the age-predicted maximal heart rate. Peak oxygen consumption (peak VO_2_) is calculated using a 30-second rolling average of breath-by-breath data obtained during the final phase of exercise.Pre-test medication management and standardised operator training: To minimise the interference of medications with metabolic measurements, and in the absence of clinical contraindications, the following washout intervals are required before CPET: at least 4 half-lives after the last dose of SGLT2 inhibitors and diuretics; and at least 24 h after the last dose of beta-blockers and other guideline-directed medical therapy (GDMT) agents. In addition, investigators and technicians at all participating centres are required to complete a standardised CPET qualification and training assessment.Central blinded adjudication: To ensure reproducibility across multiple centres, 10% of the de-identified original CPET datasets from each participating centre will be randomly selected by blinded core laboratory personnel for blinded centralised adjudication.Optimised reporting system for primary endpoint measures: In addition to body-weight-adjusted peak VO_2_ (mL/kg/min), this study will report two supplementary measures: absolute peak VO_2_ (mL/min) and percentage of predicted peak VO_2_ (%), calculated using the Wasserman/FRIEND reference equations.

#### Secondary outcomes

2.14.2

Change from baseline to 12 weeks in peak VO_2_ as assessed by CPET.NT-proBNP.Echocardiographic parameters: Cardiac structure and function assessed by two-dimensional echocardiography using the Simpson method, including left ventricular end-diastolic diameter (LVEDD), LVEF, global longitudinal strain (GLS), left atrial strain, E/A ratio, E/e‘ ratio, E-wave deceleration time (DT), left atrial volume index (LAVI), pulmonary artery systolic pressure (PASP), interventricular septal thickness, left ventricular free wall thickness, and left ventricular mass index (LVMI).New York Heart Association (NYHA) functional class.6MWT.TCM syndrome scale: Qi deficiency with blood stasis syndrome score.Major symptoms and signs: dyspnea, palpitations, chest tightness, shortness of breath, fatigue, etc.EQ-5D score.Coagulation function.

#### Safety outcomes

2.14.3

Routine blood, urine, and stool tests, electrocardiogram (ECG), liver and kidney function tests.Urine pregnancy test (for women of childbearing potential).Chest CT.Adverse events (AEs) or serious adverse events (SAEs).

### Data collection and management

2.15

eCRF completion: Data must be sourced from original documents. All data must be entered in a timely, accurate, complete, standardized, and truthful manner. No items should be left blank. Any corrections must be documented with the reason for change.eCRF review: The clinical research coordinator (CRC) will promptly complete, review, and submit the eCRF, and respond to queries raised by the data manager or clinical research associate (CRA). After data cleaning, the principal investigator will sign to confirm the data.EDC database: A study-specific EDC database will be designed. User acceptance testing (UAT) will be completed before the enrollment of the first patient. All users must complete training before accessing the database.Data entry and verification: Data will be promptly entered and submitted after each visit. The data manager and medical reviewer will review the data and issue queries. After the investigator responds to the queries, the data will be confirmed.Medical coding: Adverse events will be coded using the latest Chinese version of the Medical Dictionary for Regulatory Activities (MedDRA). Concomitant medications will be coded using the second edition of the *Dictionary of Contemporary Drug Trade Names and Aliases*.Blind review and unblinding: After all data tasks are completed, a blind review meeting will be convened to determine the analysis populations and lock the database. After the database is locked, the first unblinding will be performed, during which the statistician will be unblinded only to Group A versus Group B (without knowing which group is SXYX or placebo), followed by statistical analysis. At the final study meeting, the second unblinding will be performed with all participants (investigators, sponsor representatives, and the statistician) together, after which the study report will be signed and finalized.Wearable Device Data Collection and Management1) Device information: Maiya Smart ECG Ring (Maiya Technology, China, model TK30). The device is equipped with a high-performance ECG sensor (GH3228), a PPG sensor (GPSE1602B), and an accelerometer (SC-7A20H), and is compatible with Android 9.0 and iOS 10.0 and above. 2) Pre-trial validation study: To ensure the reliability of data obtained from the wearable device in the target HFpEF population, a pre-trial validation study will be conducted before the main trial is initiated. A total of 32 patients who meet the trial entry criteria (8 from each sub-centre) will be enrolled. Each participant will undergo standard 12-lead electrocardiography (ECG) and pulse oximetry monitoring while wearing the device. Data will be collected under two conditions: (i) at rest (10 min in the supine position), and (ii) immediately after the 6-minute walk test (6MWT). The validation will assess: (i) heart rate accuracy: Bland–Altman analysis will be performed to calculate the mean bias and limits of agreement between the device-derived heart rate and that from the 12-lead ECG; the device will be considered acceptable if the mean absolute error for heart rate is ≤5 beats/min; (ii) oxygen saturation accuracy: the device-recorded SpO_2_ will be compared with that from pulse oximetry, with an acceptable mean absolute error of ≤2%; (iii) step count (distance): device-recorded data will be compared with the actual distance walked during the 6MWT, with an acceptable mean absolute error of ≤5%. 3) Wear time: Participants will wear the ring continuously for 1 week at baseline, week 12, and week 24. To ensure adequate data acquisition, at least 4 valid days are required at each assessment time point. A valid day is defined as a day with wear time ≥23 h (objectively verified by the device's accelerometer and skin-contact sensor) and ≥8 h of valid signal recording. 4) Data quality standards: Within each valid day, at least 8 h of valid ECG/PPG recordings (excluding artefact-contaminated segments) are required. If more than 30% of the recorded signal is classified as artefact (e.g., motion artefact, poor skin contact, or electrical interference), the data from that day will be excluded from analysis. All device-derived data will be reviewed by a blinded central core laboratory, and a random 10% sample will be subjected to additional manual quality checks to ensure inter-rater reliability. 5) Handling of missing data: Multiple imputation (MI) will be employed under the assumption of conditional missing at random (MAR), given the covariates included in the analysis model (baseline values, treatment allocation, visit time) and previous observed values. The imputation model will include all covariates used in the descriptive analysis model for the wearable device data, and will incorporate auxiliary variables that influence the missingness mechanism (e.g., signal quality flags, wear logs) to improve precision. Imputation will be performed only for measures that are complete at baseline but missing at subsequent visits (week 12 or week 24) due to <4 valid days; subjects with complete baseline data missing will not be included in the primary MI analysis, but will be retained in the modified intention-to-treat (mITT) set for other endpoint analyses. Twenty imputed datasets will be generated; the descriptive analysis model will be fitted to each, and the estimates and standard errors will be pooled using Rubin's rules. To explore the potential impact of the MAR assumption on the trend of results within an exploratory framework, a worst-case exploratory scenario analysis will be conducted: missing values in the intervention group will be replaced by the group observed mean +2 standard deviations (in the direction of worsening), and those in the control group by the group observed mean −2 standard deviations (in the direction of improvement). The results of this scenario analysis will be reported descriptively, comparing whether the direction and magnitude of the effect estimates are consistent with those of the primary analysis; all results will be clearly labelled as exploratory, with no formal statistical significance testing or adjustment for multiplicity. 6) Derived outcome measures: Mean heart rate, step count (distance), oxygen saturation, heart rate variability, and nocturnal sleep duration.
